## Abstract

**Background:**

Endotracheal intubation by direct laryngoscopy is a widely performed lifesaving technique. Although there are guidelines for optimal size and depth of insertion of an endotracheal tube (ETT) for successful intubation, there is no consensus on the point at which it should be held along its length. This will arguably affect the time, ease, and success of the technique due to a difference in visualization and torque applied to the ETT after glottic visualization. We aim to compare the effect of 2 different sites of holding the ETT on time to intubation (TTI), intubation difficulty scale (IDS), and complications.

**Methods:**

ASA 1–2 patients (>18 years) posted for surgery under general anesthesia, undergoing supervised intubation by anesthesia trainees (experience < 18 months), will be included. Patients with an anticipated difficult airway or unanticipated difficulty—CL grade 3 or 4 requiring the use of airway adjuncts—will be excluded. Patients will be randomized by a computer-generated number list, and allocation concealed with opaque sealed envelopes. The two sites for holding the ETT will be group 1 at 19 cm and group 2 at 24 cm. ETT marked at the selected site will be handed by the technician once the optimum position of the table, patient, and laryngoscopic view is confirmed by the intubator. The entire procedure will be video recorded. Two blinded assessors will independently review the videos to document the time to intubation and intubation difficulty score. A postoperative sore throat will be recorded.

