### Eligibility criteria {10}

The participants included in the study will be:
i.Patient: Adult patients (age > 18 years) with ASA I to II functional status undergoing elective/emergency surgical procedures under general anesthesia who can understand and provide valid consent for the procedure. The exclusion criteria will be patients less than 18 years of age, American Society of Anesthesiologists (ASA) > 2 functional status, patients having Cormack Lehane (CL) grading more than 2 on direct laryngoscopy, use of airway adjuvants, and refusal to give consent for the study.ii.Intubator: Intervention (intubation) will be performed by trainee anesthesia residents who have less than 18 months of experience. As a part of the curriculum, training in the theory of airway management and mannikin intubations will ensure that all the trainees have experience of a minimum of 40 intubations on mannikins or patients. A consultant anesthetist will supervise all intubations per protocol.iii.Procedure: All procedures will be video recorded from the time patient is positioned after induction, and the laryngoscope is asked for, to after confirmation of correct tube position (this may be visual, auscultatory, or EtCO2 guided). Procedures where the trainee deviates from the methodology, improper table position, CL grade found > 2, use of a bougie, stellate, or other airway adjuncts, or take-over by the consultant (unanticipated difficult airway), will be video recorded but excluded from the analysis. This will reduce confounding the time to intubation due to poor visualization of the laryngeal inlet.

A few cases will be tried with a Go-Pro camera, hoping to ascertain data for the exact laryngoscopy view (with the understanding that the visual axis of the camera will not be identical to the LEI, and the forehead mounted camera might make the process more cumbersome for the trainee).

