##### Personnel

1. The consultant anesthetist and trainee will position the patient and prepare for intubation.

2. The operation theater technician (not a part of the research team) will select a sealed envelope after the patient enters the theater and the WHO checklist is completed. He will then mark the endotracheal tube at the site the patient has been randomized to19 or 24 cm with a transparent sticker.

3. A trainee technician (not a part of the research team) will be positioned in a way such that the entire process is visible and will video record the procedure.

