##### Laryngoscope

All procedures will be performed with a curved blade Macintosh laryngoscope, size ¾ as appropriate for the patient.

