#### Technique

After induction and a minimum of 3 min of administering the paralytic agent, the intubator will perform the laryngoscopy. Once the intubator declares that the CL grade is optimal (CL < 3), it will be confirmed by the faculty or senior either verbally or visually. Once declared as an “optimum laryngoscopic view,” the tube will be handed over by the technician to the intubator and prior instruction will be given to take the first attempt at the marked point, with the elbow close to the body, with the thumb at the plastic marker, index, and middle fingers opposite [2]. If the above will be difficult, then any change in methodology will be allowed as per the faculty’s decision and will be documented from the video. The whole procedure will be videographed.

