### Outcomes {12}

Primary outcome measures: time to intubation (TTI) in both groups. The TTI will be calculated from holding the ET to removing the laryngoscope—after declaring a tube passed “under vision.” The frame has been chosen to reduce bias due to laryngoscopy problems or delay due to attaching the circuits and ventilating till capnographic confirmation of correct tube position. The primary outcome will be described in seconds.

Secondary outcome measures assessed will be first-pass intubation success rate; intubation difficulty scores (IDS) [6]; ease of the intubation assessed by the intubator, faculty, and a blinded assessor unrelated to the study on the Likert scale (0—very easy to 5—extremely difficult); and incidence of complications (bleeding or sore throat) in each group. The IDS comprises of attempt (in no), additional operators (if any, then in no), alternative technique: stylet/bougie, Cormack Lehane grading (CL grade: I/II/III/IV), lifting force: normal (0)/increased (1), external laryngeal pressure required during insertion of the tube: no (0)/yes (1), and position of vocal cords: abducted (0)/adducted (1).

Assessments from the video footage: These assessments will be done by two different anesthesiologists independently. The mean values will be used for analysis after disputes/disagreements (if any) are settled by a third person not belonging to the research team. This will reduce bias due to possible errors in time calculations.

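### The stated source of the IDS, a video shot from within the room, cannot show at least two of the scale's seven items

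*Protocol article*

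**What the plan says.** All places are in the protocol article.

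- **Rater and source.** Abstract, Methods: "Two blinded assessors will independently review the videos to document the time to intubation and intubation difficulty score".
- **Video.** Under Personnel, a trainee technician "will be positioned in a way such that the entire process is visible and will video record the procedure". Under Laryngoscope: "All procedures will be performed with a curved blade Macintosh laryngoscope". This is direct laryngoscopy, so the blade itself gives no image to record.
- **The view down the blade.** Eligibility criteria {10}: "A few cases will be tried with a Go-Pro camera, hoping to ascertain data for the exact laryngoscopy view". The same sentence accepts that the camera's axis will differ from that of the laryngoscopy.
- **Items.** Outcomes {12} lists seven: attempts, additional operators, alternative technique, CL grade, lifting force, external laryngeal pressure and cord position. Those at issue read "Cormack Lehane grading (CL grade: I/II/III/IV), lifting force: normal (0)/increased (1" and "position of vocal cords: abducted (0)/adducted (1".
- **Sequence.** Technique: "Once the intubator declares that the CL grade is optimal (CL < 3), it will be confirmed by the faculty or senior". The tube, and with it the allocated grip, comes only after this.
- **Exclusions.** Eligibility criteria {10} removes from the analysis cases with CL above 2, airway adjuncts or consultant take-over. The dropout criteria remove laryngeal pressure (BURP) applied once the tube is held.

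**The concern.** The article names a rater, a source and a list of items, and the three do not fit together. A reader of a room video has no sight of the cords, and no direct sight of whether the view was grade I or II. Unless the values reach the readers by some route that the article does not describe, they will be inferred or left to each reader's impression. Averaging two readers, with a third person for disputes, cannot recover what none of them can see.

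Timing is a second difficulty. The trial asks what grip site does once a good view has been obtained, and TTI starts at tube holding so that laryngoscopy problems stay out of it. The IDS nevertheless carries the CL grade, which exists before the grip does.

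At stake is the meaning of the IDS comparison. Poorly measured items add noise. A score with little room to move could produce a null result that is then reported as showing no effect of grip on difficulty.

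**Working it through.** The plan gives no figure on this point, so nothing needs to be reproduced. The check takes each of the seven items in Outcomes {12} and asks two questions. Can a video shot from the room show it? Can it still respond to grip site in the restricted analysis set (after the exclusions in Eligibility criteria {10} and the dropout criteria)?

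| IDS item | Visible on room video? | Room to respond to grip in the restricted set |
|---|---|---|
| Attempts | Yes | Yes |
| Additional operators | Yes | Little: consultant take-over is excluded |
| Alternative technique | Yes | Little: bougie, stylet and other adjuncts are excluded |
| CL grade | No, beyond a possibly audible statement that it is below 3 | Initial value set before hand-over; only I or II remain |
| Lifting force | At best inferred | Possible: timing not stated, may change as the tube passes |
| External pressure | Yes | Little: BURP after the tube is held is dropped |
| Cord position | No | Possible: timing not stated, may change as the tube passes |

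Counts:

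- Not visible: CL grade (I versus II) and cord position, 2 of 7 (2/7 = 29%).
- Not visible or only inferable, adding lifting force: 3 of 7 (3/7 = 43%).
- Visible: 7 − 3 = 4 items. The exclusions largely remove the variation in 3 of these, which leaves 4 − 3 = 1, number of attempts, as the main item both visible and free to respond to grip.

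These are counts of items, not shares of the score. The article does not say how CL grade is converted to points, so no figure in IDS points can be derived.

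The spoken declaration does not close the gap. The Technique section requires only that the view be stated as below grade 3 and confirmed aloud or by looking. That establishes eligibility but does not separate I from II, and it says nothing about force or cords.

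**The case against.** The strongest reply is that video may not be the only source. The explicit statement stands in the abstract. Outcomes {12} justifies double reading by errors in timing and does not list the IDS among the video assessments. The timeline puts the IDS in the intubation column, whereas the blinded assessor's ease rating comes after extubation. Clinical data go on a paper CRF that is not shown, and an article may leave item-level sourcing to that form.

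This does not remove the point. The abstract states a rule, and the body does not contradict it. The timeline does not decide the matter, because the time of holding the tube, which assessors take from the video, sits in the same intubation column. If unblinded theatre staff do complete these items on the CRF, they are not the blinded assessment that the abstract promises.

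Several parts of the reply do stand, and they rule out stronger readings:

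- *That three items cannot be scored at all.* An experienced anesthesiologist may partly infer lifting force from the video, and the recording covers the period in which the view is declared.
- *That all three are insensitive to grip.* Only CL grade is explicitly set before hand-over. The Background section suggests that the gripping hand may obstruct the view, and that trainees must control the laryngoscope with one hand while the other guides the tube. Force and cord position may therefore change after the grip begins.
- *That a subscore of visible items should replace the IDS.* In the restricted set it would come down largely to number of attempts, which nearly duplicates first-pass success, already a secondary outcome.
- *That the comparison is biased by pre-hand-over variation.* Randomization balances this in expectation, so it costs precision rather than validity.

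**Conclusion.** The point holds as a mismatch between source and items in a secondary outcome. At least two of the seven IDS items cannot be read from the stated source and a third can only be inferred. One of the unseen items, CL grade, has an initial value fixed before the intervention.

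This rests on two assumptions: that the routine video is the room recording described under Personnel, and that the readers receive nothing beyond it and its sound. The article's use of a head-mounted camera to seek the laryngoscopic view supports the first.

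A reader might go further and infer that the main secondary endpoint is compromised, that a fixed number of IDS points is spurious, or that the IDS will simply echo TTI. The documents support none of these. The IDS is one of four unranked secondary objectives, the CL scoring is not given, and a dependence on TTI is conceivable but not shown.

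The caution about a null IDS applies chiefly to the restricted analysis. Section {20c} also promises an intention-to-treat analysis. If excluded cases re-enter there, the operator, technique and pressure items can vary again.

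**What to change.** Amend the abstract's Methods paragraph and Outcomes {12} so that each IDS item has a named rater and source:

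1. When the view is declared, the intubator records the exact CL grade on the CRF and the supervisor confirms it.
2. Immediately after tube passage, lifting force and cord position are recorded on the CRF in the same way. Recording them earlier would lose any change that occurs while the tube is passed.
3. The blinded video readers score TTI and the four visible items: attempts, operators, alternative technique and external pressure.
4. The report gives the full IDS with an item-level table by group, and shows CL grade at declaration as a pre-intervention descriptor.
5. The report states that a null IDS in the restricted set is not evidence of no effect on difficulty, because the exclusions remove most cases in which the visible items other than attempts could vary.

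The cost is three CRF entries and some changed wording. There are two drawbacks. The bedside items come from unblinded staff, which matters most for force and cord position because these are recorded after the grip is known. Recruitment is already under way, so patients enrolled so far may lack the entries; their number should be reported.

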**Sample size:**

To detect a 20% difference in time to intubation between groups with a significance level of 5% and power of 85%, we will need a total of 298 patients. Accounting for data loss, we plan to recruit 180 patients in each group.

**Discussion:**

This will be the first study to assess whether the site of holding the tube has any impact on the ease and time taken for intubation. The findings of this study will provide scientific evidence for suggesting an appropriate place for holding the ETT during direct laryngoscopy procedures.

**Trial registration:**

Clinical Trials Registry India CTRI/2019/09/021201

## Introduction

### Background and rationale {6a}

Laryngoscopic endotracheal intubation (LEI) is a fundamental procedure for securing the airway, performed for resuscitation in emergency scenarios or elective conditions such as general anesthesia. Successfully placing the endotracheal tube (ET) in the trachea is a skill learned over time. Successful intubation by anesthesiology trainees has been defined by Konrad et al. [1] as “adequate technical performance” without any staff assistance. Traditional teaching guides trainees from available evidence on the optimal position of patients’ head and neck [2], the size and depth of the endotracheal tube [3, 4], type of laryngoscope blade [5], method of laryngoscopy, and direction of bevel for intubation success [6].

This study’s senior investigator has more than 20 years of experience as a teacher of graduate and post-graduate trainees (medical and paramedical) in emergency medicine, anesthesia, and critical care. Over years of witnessing thousands of laryngoscopic intubations, she observed that more experienced personnel hold the ET farther away from the patient-end than do trainees. Discussions among peers confirmed that others shared her opinion. The consensus was that by learning from the experience of multiple intubations, experienced personnel realized (subconsciously) that the further the tube is held from the tip,
The better is the resultant glottic view—the right hand gripping the tube has a lesser chance of coming in the field of vision during the wrist movementsThe easier it is to fine-adjust the movement of the tip of the ET close to the glottis. As the pivot (point of rotation of the tube, usually the thumb) moves away from the tip, the negative torque exerted by the distal part of the ET decreases, thereby making it easier to manipulate and guide it into the glottic opening (Fig. 1)

**Fig. 1 Fig1:**
[figure not shown]
Figure illustrating how the torque varies with the point at which the endotracheal tube is held ( P1, 2, 3); as thedistance from the tip increases ( P3), lesser is the torque making for easier fine adjustments to the movements ofthe tube tipWith inexperienced trainees, juggling between maintaining the forces and torque on the laryngoscope with the left hand and coordinating the right-handed movements might make the process more difficult [7]

A literature search resulted in only one mannikin-based study: it hypothesized that the position of holding the tube would logically affect the path of vision and torque applied to the ET during the procedure. The farther the tube is held, with the elbow close to the chest, the greater the positive torque will be generated when the cuff passes the incisors, affecting the ET tip’s tilting angle [3]. There is no data available in human studies. Experts hold the ET at an optimal position by virtue of their experience. However, without evidence and guidelines for the optimal position, trainees tend to hold it over a range of places.

We aim to compare the time for intubation, complications, and the success of LEI performed by trainees, between two groups: one holding the ETT at 19cm from the tip and the other at 24 cm .

### Objectives {7}

#### Aims

To find if the place where the ET is held (site) affects LEI after a good laryngoscopic view is attained.

#### Objectives

##### Primary objective

To compare the time to intubation (TTI) between two groups of trainees holding the ET at two different (predetermined) sites.

##### Secondary objectives

To compare between the groups

● Rate of success of first-pass intubation

● Intubation difficulty score (IDS)

● The subjective ease of intubation, as assessed by the trainee, the supervising anesthetist, and a blinded assessor

● Airway-related complications

### Trial design {8}

This will be a randomized, controlled, surgeon-, patient-, and assessor-blinded single-center equivalence trial with two parallel groups and a primary endpoint of time to intubation during direct laryngoscopy for general anesthesia. Randomization will be performed as simple randomization with 1:1 allocation.

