### Sample size {14}

Based on the pilot study, the mean time to intubation was found to be 8.83 s, a standard deviation of 4.07 s, and a variance of 16.57 s. Using this information—an allocation ratio of 1:1, to ascertain a 20% difference in time to intubation between the two groups, it was calculated that a sample size of at least 149 participants in each group is necessary to detect a difference of 1 s in time to intubation in between the groups, if we allow a significance level of 5% and power our study at 85%. Thus, a total sample size to demonstrate the minimum effect size is 298, and assuming approximately 20% loss and rounding up to the nearest number, the total sample size required is 360 (180 in each group). The calculation was done using online sample size calculators http://powerandsamplesize.com and http://www.sample-size.netusing comparison of means for two-sided equality and the normal approximation using the *Z* statistics instead of the *T* statistics. The calculated sample size was concordant between the two calculators used.

We felt a 20% difference in time to intubate (TTI) as defined by us in the study would be clinically significant, as this difference means greater manipulations after the tube is inside the oral cavity resulting in more significant trauma and complications of intubation.

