### Statistical methods

#### Statistical methods for primary and secondary outcomes {20a}

A researcher blinded to the group allocation will perform the statistical analysis of all randomized patients using the SPSS for Windows software (ver. 26.0; SPSS Inc., Chicago, IL, USA) on completion of the study.

Flowchart

For presenting the demographic data, the categorical data (like gender, SA status, gender) will be presented as a percentage of the total, while the quantitative data will be presented as means or medians with standard deviations or interquartile range. The data will be tabulated with standardized differences reported between groups.

The primary outcome will be described in seconds. The descriptive statistics that will be used is a standardized difference of means or proportions accordingly. All the secondary outcomes data, namely time to intubation and the IDS, are quantitative and will first undergo a normality test either the Shapiro-Wilk test or the Kolmogorov-Smirnov test to check the normality of the quantitative variables’ distribution. After this, the Mann-Whitney *U* test or independent *t*-test will be used, depending on whether the data is parametric or non-parametric, including the primary outcome variables. Accordingly, the data will be represented as mean with standard deviation or median with interquartile range.

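### The protocol calls the study an equivalence trial but sizes and tests it for a difference with no margin, so a non-significant result could not support equivalence

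*Protocol article*

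**What the plan says.** The framework is stated once, under Trial design {8}: "assessor-blinded single-center equivalence trial with two parallel groups". The other sections that fix the design read differently.

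- Primary objective: "To compare the time to intubation (TTI) between two groups of trainees holding the ET at two different (predetermined) sites". It does not aim to show that the sites are alike.
- Sample size {14}: the calculators were run for "comparison of means for two-sided equality and the normal approximation". The target is given as "to ascertain a 20% difference in time to intubation between the two groups" and, in the same sentence, the resulting size "is necessary to detect a difference of 1 s in time to intubation". The Abstract also sizes the trial to detect a 20% difference.
- Statistical methods {20a}: the Mann-Whitney U test or independent t-test "will be used, depending on whether the data is parametric or non-parametric, including the primary outcome variables".

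No equivalence margin, two one-sided tests procedure or confidence-interval criterion is given. Sample size {14} calls a 20% difference clinically significant, as something to detect. It does not call it a margin.

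**The concern.** Equivalence and difference trials have opposite null hypotheses. An equivalence trial must reject a difference as large as the margin. A difference trial must reject no difference. The protocol declares the first and fixes the sample size and the test for the second. This is not detail left to an analysis plan: any later plan would have to contradict either the design statement or the sample size and test.

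The stake is the wording of a null result. The trial is meant to inform where trainees should hold the tube. A p-value above 0.05 in a trial labelled equivalence could be reported as showing that the two sites are interchangeable, which the planned test cannot show.

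**Working it through.** **Inputs, all from Sample size {14}.** "the mean time to intubation was found to be 8.83 s, a standard deviation of 4.07 s"; two-sided 5% significance; 85% power; 1:1 allocation; 149 per group, 180 per group after allowance for loss. Twenty per cent of the mean is 0.20 × 8.83 = 1.766 s.

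**1. The stated sample size.** For two-sided equality with the normal approximation, n per group = 2 × [SD × (1.960 + 1.036) / difference]².

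- Difference 1 s: 298 per group.
- Difference 1.766 s: 96 per group.

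Neither gives 149. The same expression without the factor 2 (a one-sample formula) gives 149 at 1 s. So 149 is not explained by the stated two-sample inputs. That is a separate matter, but it shows that the 20% and 1 s targets are not the same target.

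**2. What a non-significant result leaves open.** SE = 4.07 × √(2/149) = 0.4715 s. The largest difference that is still non-significant is 1.96 × 0.4715 = 0.92 s. Its 95% interval reaches 0.92 + 0.92 = 1.85 s, above both 1 s and 1.77 s.

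This depends on the number analysed. The upper end is 3.92 × 4.07 × √(2/n):

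| Analysed per group | Upper 95% limit at a just non-significant difference |
|---|---|
| 144 (180 less 20%) | 1.88 s |
| 149 | 1.85 s |
| 180 (no loss) | 1.68 s |

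With no loss at all the limit falls inside 1.77 s. It stays well outside 1 s in every row.

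**3. What an explicit margin could support.** The protocol states no margin, so its two effect sizes are used here as assumed margins M. Power at zero true difference, requiring the 95% interval to lie within ±M, is 2Φ(M/SE − 1.96) − 1.

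- M = 1.766 s: 2Φ(3.745 − 1.960) − 1 = 0.926.
- M = 1 s: 2Φ(2.121 − 1.960) − 1 = 0.128.

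With a 90% interval (1.645 in place of 1.96) the figures are 0.964 and 0.366. The choice between 1.77 s and 1 s therefore decides whether the trial could support a claim of no relevant difference.

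**The case against.** The best reply is that this is one wrong word. The label appears once, the rest of the text coherently describes a difference trial, and the study can be run and analysed as written. Nowhere does the article say that p>0.05 will be read as equivalence. That is correct: the misreading is a risk the label creates, not a stated rule. It does not rescue the label, which names a property the design lacks.

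Three stronger readings are tempting, and the document does not support them.

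- *The label causes a high rate of false equivalence claims.* If the sites truly differ by 1 s, the planned test is non-significant in about 44% of trials at 149 per group. That is type II error from too few patients for 1 s, and relabelling leaves it unchanged. A 1 s difference would also lie inside a ±1.77 s margin. At a true difference of 1.77 s the test misses only about 4% of the time.
- *The 20% threshold is already a justified margin.* It is justified as a difference worth detecting, and the same sentence also puts the target at 1 s.
- *An equivalence claim is available at no cost.* This holds only if the larger of the two values is chosen.

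**Conclusion.** The design label contradicts the objective, the sample size and the primary test, and no margin is stated. A non-significant result cannot by itself support equivalence: at 149 per group it is compatible with a difference of up to about 1.85 s. The contradiction rests on the text alone and needs no assumption.

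The figures assume the pilot SD of 4.07 s, a normal approximation and about 149 analysed per group. The only pilot described, in the explanation for the site of holding, observed experienced anesthesiologists. If the SD came from that pilot, trainees may vary more, and the intervals would be wider. The overshoot beyond 1.77 s is narrow and disappears if all 180 per group are analysed. The overshoot beyond 1 s does not.

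**What to change.** In Trial design {8}, replace the word equivalence with two-sided superiority, and add that p>0.05 will not be reported as showing equivalence.

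If the sponsor also wants to be able to claim no clinically relevant difference, three further steps are needed:

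- reconcile the 20% (1.77 s) and 1 s targets in Sample size {14};
- adopt one value explicitly as a margin, with a reason, before results of the interim analysis (Interim analyses {21b}) are seen;
- require the whole 95% confidence interval for the difference in seconds to lie within that margin, whichever of the two tests supplies the p-value.

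The sponsor should do this knowing that power at 149 per group is about 93% for ±1.77 s and about 13% for ±1 s.

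The cost is a protocol and registry amendment through the approvals listed in section {25}, because recruitment is under way. Relabelling needs no extra patients.
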